### Safety assessment

2.7

We will closely monitor the safety of heat-sensitive moxibustion throughout the study. Any adverse events (AEs) that are not related to the natural progression of hypertension will be recorded and reported to the Ethics Committee regularly. If a serious AE that leads to hospital admission, disability, a threat to life, or death occurs, we will report it to both the Ethics Committee and the Food and Drug Administration of Jiangxi Province within 24 hours.

We will also assess to what degree each AE is related to heat-sensitive moxibustion according to the following considerations^[19]^:

(1)whether there are time and position correlations between the AE and heat-sensitive moxibustion;(2)whether the AE cannot be explained by other factors;(3)whether the AE is alleviated or disappears when heat-sensitive moxibustion is stopped;(4)whether the AE reappears when heat-sensitive moxibustion is administered again; and(5)whether the AE can be explained by biological or pharmacological mechanisms.

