### Study visits

2.8

During the 1-year follow-up period, the investigators will visit the patients monthly at the community health service centers, which are generally within 1 km of the patients’ homes. At month 0 (baseline visit), we will collect demographic characteristics (name, phone number, sex, age, education level, height, and weight) and disease-related characteristics (SBP, DBP, course of hypertension, comorbidities, smoking, drinking, and type and dosage of antihypertensive drugs currently used). At months 6 and 12, we will measure blood pressure, changes in doses of antihypertensive drugs, quality of life, blood and urine indicators, and AEs. The other regular visits (ie, months 1–5 and 7–11) will involve the distribution of moxa rolls and moxibustion boxes to patients, the assessment of patient compliance and the adjustment of the doses of antihypertensive drugs. A detailed schedule of the study visits is shown in Figure 2.

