### Compliance enhancement

2.9

By default, we will provide patients in the heat-sensitive moxibustion group with 120 moxa rolls and 4 moxibustion boxes for free each month. If the moxibustion materials are insufficient because some are lost or for other reasons, patients can apply to receive more materials for free. When the patients return for a visit, they need to return the moxibustion box used last month to receive new moxibustion boxes. The investigators will determine whether the dose of moxibustion reported by the patients is consistent with the degree of blackening of the moxibustion boxes by the soot produced by burning the moxa. Patients in both groups will receive free health consultations and physical examinations at each visit and a reward of 100 and 200 Chinese yuan when the 6- and 12-month visits are completed, respectively. Of course, patients can voluntarily withdraw whenever for whatever reason during the study, and withdrawal will not affect any subsequent treatment.

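### Section 2.8 schedules adverse event assessment at months 6 and 12 but not at the other ten monthly visits, which fits poorly with the continuous safety monitoring promised in section 2.7

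*Protocol article*

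**What the plan says.** Section 2.8 (Study visits) sets the contact frequency: "the investigators will visit the patients monthly at the community health service centers", for one year. It then gives the content of the follow-up visits in two lists.

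- Months 6 and 12: "At months 6 and 12, we will measure blood pressure, changes in doses of antihypertensive drugs, quality of life, blood and urine indicators, and AEs".
- Months 1–5 and 7–11: distribution of moxibustion materials, then "the assessment of patient compliance and the adjustment of the doses of antihypertensive drugs". AEs are not in this list.

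Where the two lists meet, the text reads: "blood and urine indicators, and AEs. The other regular visits (ie, months 1–5 and 7–11) will involve the distribution of moxa rolls".

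The section closes by pointing to a figure: "A detailed schedule of the study visits is shown in Figure 2". That figure is not reproduced in the text under review.

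Section 2.7 (Safety assessment) opens with a broader commitment: "We will closely monitor the safety of heat-sensitive moxibustion throughout the study". It says that AEs other than those from the natural course of hypertension will be recorded and regularly reported to the Ethics Committee, and that serious AEs will be reported within 24 hours. It lists five considerations for judging relatedness. They include the match in time and position, improvement when moxibustion stops, and "whether the AE reappears when heat-sensitive moxibustion is administered again".

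Section 2.9 (Compliance enhancement) gives both groups a health consultation and a physical examination at each visit, and states that "patients can voluntarily withdraw whenever for whatever reason during the study".

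**The concern.** The two sections do not say the same thing about when AEs are ascertained. Section 2.7 describes a continuous process. Section 2.8 attaches AE measurement to two dates six months apart and gives the visits in between a different content.

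The relatedness criteria in section 2.7 need an onset date, a body site and a record of when sessions were stopped and restarted. These are hard to obtain at a scheduled enquiry months after the event. The hazard that the article itself names is burns (sections 2.4 and 2.5), and a minor burn may have healed by the next scheduled assessment.

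Safety is a stated aim in the Introduction. The Discussion presents the study as groundwork for later randomised trials, partly because prior safety evidence is lacking. Section 2.10 also lets the data monitoring committee stop the study on interim safety results, with six months of follow-up as its example. At that point each patient would have had one listed AE assessment. An event that was never asked about cannot be recovered in the analysis.

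**Working it through.** The plan states no figure on this point, so there is nothing to reproduce. The check compares the texts and adds simple arithmetic for scale.

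**1. Share of visits with a listed AE assessment (section 2.8).** Post-baseline visits are months 1 to 12, which is 12. Visits listing AEs are months 6 and 12, which is 2. Visits not listing them: 12 − 2 = 10, and 10/12 = 83%.

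**2. Length of the scheduled recall window.** From baseline to month 6 and from month 6 to month 12 is 6 months each. At the suggested one session a day (section 2.5), that is about 6 × 30 = 180 self-administered sessions. This is a ceiling on the suggested schedule, since section 2.5 lets patients adjust their dose. With an AE question at each visit, there would be 12 scheduled enquiries instead of 2, and the longest scheduled window would fall from 6 months to 1.

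**3. Patients who may leave before any scheduled AE enquiry.** Inputs: 300 planned per group and 20% attrition (both section 2.11). Applying the 20% to the enlarged sample is an assumption. Leavers per group: 0.20 × 300 = 60. The article does not say when they leave, so the share leaving before month 6 is assumed:

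| Assumed share of leavers going before month 6 | Patients per group | Share of 300 |
|---|---|---|
| 25% | 60 × 0.25 = 15 | 5% |
| 50% | 60 × 0.50 = 30 | 10% |
| 75% | 60 × 0.75 = 45 | 15% |

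These are upper limits on the patients affected. Most of these patients may have had no AE, and section 2.7 allows an AE to be recorded outside the listed visits.

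**4. What covers the gap.** Three provisions could capture an event between months 0 and 6 or between months 6 and 12.

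- The general recording commitment in section 2.7 says which events are recorded. It does not say when or how patients are asked.
- The 24-hour rule in section 2.7 covers serious events only, so a minor burn would not qualify.
- The consultation and examination in section 2.9 take place at each visit, but the article does not link them to AE recording.

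Each leaves a route for an event to be noted. None schedules an enquiry.

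**5. Comparability of the groups.** Of the three tasks listed for the intermediate visits, material distribution and moxibustion compliance concern only the moxibustion group. Unprompted capture may therefore differ between groups. The article does not settle the direction: more talk about moxibustion could raise recording in that group, while loss of patients harmed by it could lower it.

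**The case against.** The strongest reply is that the lists in section 2.8 are summaries, so that leaving an item out does not exclude it. The article supports this. Section 2.6.1 has community doctors adjust drugs at each regular visit on the past month's blood pressure, although section 2.8 lists blood pressure only at months 0, 6 and 12. Section 2.9 supplies materials every month, although section 2.8 lists distribution only for the other months. The examinations at each visit in section 2.9 do not appear in section 2.8 at all. Figure 2 is named as the detailed schedule and may list AEs monthly. A journal article also commonly leaves AE form content and withdrawal procedures to the full protocol.

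Much of this stands. A reader might infer from section 2.8 that AEs are collected only at months 6 and 12, and that events in early withdrawers are never recorded. The documents do not support that reading. Section 2.7 commits to recording AEs throughout, patients are examined at each visit, and no sentence says that withdrawers' events are discarded. Nor do the documents allow a statement that the AE rate will be biased by a known amount, or a figure for how many events six-month recall would lose.

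The reply does not remove the inconsistency. Section 2.8 expressly names AEs for one set of visits and gives the other set its own content without them. If Figure 2 does list AEs monthly, the text of section 2.8 disagrees with it and still needs correcting.

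**Conclusion.** The point holds in a limited form. As written, scheduled AE assessment falls at 2 of 12 post-baseline visits, and sections 2.7 and 2.8 do not agree on when AEs are ascertained. Non-serious, short-lived events between those visits depend on unprompted recording and may be under-recorded. At most about 15 to 45 patients per group may leave before any scheduled AE enquiry, assuming that the 20% attrition applies to 300 per group and that a quarter to three quarters of it falls before month 6.

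Severity is moderate. The general recording commitment and the monthly contact reduce the risk, and the unseen Figure 2 may already resolve it. The conclusion is about what is scheduled. It makes no claim about how many events would be missed or which group would be affected more.

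**What to change.** In section 2.8, add one standard AE question to every monthly visit and to the point of withdrawal, worded the same in both groups. The answer should record the onset date, the site, and whether sessions were stopped or restarted, so that the section 2.7 criteria can be applied. Then reconcile sections 2.7 and 2.8 with Figure 2. If the figure already lists AEs monthly, correcting the text of section 2.8 and adding the withdrawal enquiry is enough.

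The cost is a short addition to the case report form and a few minutes at visits that already take place; no new monthly visits are needed. The reported AE count will probably rise, and the report should explain this as more complete ascertainment. The change should be settled before enrolment, because events not asked about at the time cannot be reliably reconstructed.

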### Compliance enhancement

2.9

By default, we will provide patients in the heat-sensitive moxibustion group with 120 moxa rolls and 4 moxibustion boxes for free each month. If the moxibustion materials are insufficient because some are lost or for other reasons, patients can apply to receive more materials for free. When the patients return for a visit, they need to return the moxibustion box used last month to receive new moxibustion boxes. The investigators will determine whether the dose of moxibustion reported by the patients is consistent with the degree of blackening of the moxibustion boxes by the soot produced by burning the moxa. Patients in both groups will receive free health consultations and physical examinations at each visit and a reward of 100 and 200 Chinese yuan when the 6- and 12-month visits are completed, respectively. Of course, patients can voluntarily withdraw whenever for whatever reason during the study, and withdrawal will not affect any subsequent treatment.

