### Interventions and co-interventions

2.5

Patients in the heat-sensitive moxibustion group will self-administer heat-sensitive moxibustion for one year while maintaining their original antihypertensive drugs. With the doctors’ help, the patients will first identify the heat-sensitive acupuncture points near CV8 (Shenque, the center of the navel), CV4 (Guanyuan, approximately 10 cm below the navel), and bilateral ST36 (Zusanli, approximately 7 cm below the lateral of the knee) and then perform moxibustion on the heat-sensitive acupoints. Self-sticking mini-moxa rolls will be used as the combustible material, which can be placed and burned in a moxibustion box (Fig. 2). A matching velvet bag can be used to wrap the moxibustion box to avoid burns. The suggested dose of moxibustion will be one moxa roll (approximately 30 minutes) per session, with 1 session per day and 7 sessions per week. Driven by a pragmatic design, we will allow the patients to adjust the dose of moxibustion to make it convenient, but they need to truthfully report the adjusted dose. Patients in the control group will only maintain their original antihypertensive drugs and will not perform heat-sensitive moxibustion. There will be no restriction on the type and dose of antihypertensive drugs, but other acupoint stimulation therapies, such as acupuncture, will be prohibited.

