#### Secondary outcomes

2.6.2

(1)Quality of life will be assessed by a validated patient-reported outcome scale,^[18]^ which includes 27 items and assesses the impacts of hypertension on the 3 dimensions of quality of life, namely, the physical dimension (18 items), psychological dimension (4 items), and family-social dimension (5 items). Each item is divided into 5 categories, with each category receiving 0 to 4 points in sequence. A higher score indicates a worse quality of life. The total score equals the sum of the score of each item, ranging from 0 to 108 points. The detailed content of the scale is provided in the Supplemental Content (http://links.lww.com/MD/E870). We will also analyze the scores of individual dimensions separately.(2)Indicators related to diabetes mellitus, including changes in fasting blood glucose (mg/dl) and hemoglobin A1c (%), will be assessed.(3)Indicators related to dyslipidemia, including changes in total cholesterol (mg/dl), triglycerides (mg/dl), low-density lipoprotein cholesterol (mg/dl), and high-density lipoprotein cholesterol (mg/dl) levels, will be assessed.(4)Indicators related to hypertensive renal disease, including urinary albumin (g/l) and serum creatinine (μmol/l) levels, will be assessed.(5)Patient compliance will be determined. Patient compliance will be deemed poor if a patient administers heat-sensitive moxibustion fewer than 8 times per month. The proportion of patients with poor compliance will be assessed.

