### Data management and monitoring

2.10

All investigators will receive training in standardized operating procedures before the study starts. Data will be collected by community doctors using pilot-tested case report forms. Each patient's informed consent form and case report forms will be bound into 1 volume for management. The distribution of the moxa rolls and moxibustion boxes will also be strictly recorded. The software used to manage the electronic database will be Microsoft Access version 2016 (Microsoft Corporation, US), and the data will be doubly input and cross-checked by 2 independent investigators. All data in the database will be anonymized. When performing data analysis, the grouping will be concealed from the analysts.

An independent data monitoring committee will be established to monitor the quality of the data collection (eg, whether there are any incorrectly reported or missing data) and to ensure that any amendments or incomplete data are addressed in a timely manner. The committee will also have the right to plan an interim analysis (eg, when all patients have completed 6 months of follow-up) and to decide whether to discontinue the study based on the efficacy and safety results of the interim analysis.

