### Statistical analysis plan

2.12

The analyses of the primary outcomes will be performed in the intention-to-treat population where either patients in the control group who performed heat-sensitive moxibustion or patients in the heat-sensitive moxibustion group who stopped moxibustion during follow-up will still be kept in their original group. Meanwhile, we will also perform sensitivity analyses using the perprotocol population to test the robustness of the main analysis. All analyses of the secondary outcomes will be performed in the per-protocol population. We will decide whether to impute missing data and which method should be used to impute missing data based on the actual distribution of the missing data.

For categorical or ordinal variables, we will calculate frequencies and percentages as the descriptive statistics and compare the between-group differences using the chi-square test or the linear-by-linear association test. We will present the means with standard deviations/errors and medians with interquartile ranges for continuous variables with normal and skewed distributions, respectively; the independent *t* test or the Mann-Whitney *U* test will be used to compare 2 groups. The effects of heat-sensitive moxibustion on the outcomes will be inferred using analysis of covariance or a logistic regression model adjusted for age, course of hypertension, baseline SBP, comorbidities, education level, smoking status, drinking status, and types of antihypertensive drugs recoded as dummies. The effects will be measured as the mean difference or odds ratio with a 95% confidence interval, and *P*-values will also be calculated. In addition, we will test 2 subgroup hypotheses:

(1)the dose of moxibustion: ≥3 sessions/wk vs <3 sessions/wk;(2)whether the heat-sensitive sensation appears: yes vs no.

The significance level indicating a difference between groups and subgroups will be α = 0.05. We will use R version 4.0.2 (The R Foundation for Statistical Computing, Austria) to run all statistical analyses.

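### Session counts are self-reported and checked only by an ungraded look at soot, so classification at 8 sessions a month and 3 a week is open to over-reporting

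*Protocol article*

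**What the plan says.** All references are to the protocol article.

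- **Source of the count.** Interventions and co-interventions suggests "one moxa roll (approximately 30 minutes) per session, with 1 session per day and 7 sessions per week". It then makes the dose flexible: "we will allow the patients to adjust the dose of moxibustion to make it convenient, but they need to truthfully report the adjusted dose".
- **Check on the count.** Under Compliance enhancement, investigators decide whether the reported dose "is consistent with the degree of blackening of the moxibustion boxes by the soot produced by burning the moxa". To receive fresh boxes, "they need to return the moxibustion box used last month to receive new moxibustion boxes". The section does not mention bringing back unused rolls.
- **Supply.** The default issue is "120 moxa rolls and 4 moxibustion boxes for free each month", with more available free on request. Data management and monitoring adds: "The distribution of the moxa rolls and moxibustion boxes will also be strictly recorded".
- **Use of the count.** Under Secondary outcomes, compliance is poor if a patient "administers heat-sensitive moxibustion fewer than 8 times per month", and the proportion of such patients is an outcome. The Statistical analysis plan section sets a dose subgroup at "≥3 sessions/wk vs <3 sessions/wk".
- **Weight placed on compliance.** The Discussion presents feasibility of long-term self-administration as a major aim and says that poor compliance would count against the strategy.

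**The concern.** Both classifications need a number of sessions, set against a sharp cut. That number comes from the patient, and the one stated check is a judgement by eye with no scale attached. The distribution log does not fill the gap: it records what was handed out, and the default issue is the same whatever the patient burned.

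Over-reporting is plausible in this setting. Patients choose the therapy after lectures on its expected benefit, and the community doctors who train them also collect the data. If low users report more sessions than they performed, the poor-compliance proportion falls and some of them move into the higher-dose subgroup. The first error would make the strategy look more feasible than it is. The second would blur any relation between dose and effect. Roll counts that are not taken during follow-up cannot be recovered afterwards.

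**Working it through.** The plan states no figure on the accuracy of the check, so there is none to reproduce. The check below puts the cuts on one scale, asks what the described measures could show, and tests whether rolls could serve as a count.

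**1. The two cuts on one scale (30-day month)**
- 8 a month: 8 ÷ (30/7) = 1.87 a week.
- 3 a week: 3 × 30/7 = 12.86 a month, so the cut falls between 12 and 13.
- Suggested dose: 7 a week, or 30 a month.

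**2. What the soot judgement would have to separate at the cuts**
- 7 from 8 sessions: 1 − 7/8 = 12.5% fewer burns.
- 12 from 13 sessions: 1 − 12/13 = 7.7% fewer burns.
- The article does not say how use is spread over the 4 boxes. Eight sessions mean 8/4 = 2 burns per box if one box is used each time in rotation, and 8 per box if all four are used every time. So the same session count can mean a fourfold difference in burns per box.

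The article gives nothing to show that a visual judgement can make these distinctions.

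**3. Whether supply or roll use can stand in for sessions**
- At one roll per session, 30 sessions use 30 of the 120 rolls issued and leave 90. Issue therefore says little about use.
- 120 rolls ÷ 30 days = 4 rolls a day, which fits one roll at each of four points (also an assumption). Then 30 sessions use 120 rolls and 8 sessions use 32.
- The article does not reconcile these two readings, and a roll count depends on which applies to the patient. If a patient burns 4 per session and the rule assumes 1, then 7 true sessions use 28 rolls and imply 28 sessions, so the count never limits the report. If a patient burns 1 and the rule assumes 4, then 30 true sessions imply 30/4 = 7.5, and a fully adherent patient is classed as poor.
- Dividing by the patient's own rolls per session removes both failures: 28/4 = 7 and 30/1 = 30.

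**4. How misclassification would carry through (all inputs assumed)**

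Reported poor share = p × sens + (1 − p) × (1 − spec), where p is the true share. Take sensitivity 0.5 to 0.9 and specificity 0.90 to 0.98.
- p = 20%: from 0.2 × 0.5 + 0.8 × 0.02 = 11.6% to 0.2 × 0.9 + 0.8 × 0.10 = 26%.
- p = 30%: from 0.3 × 0.5 + 0.7 × 0.02 = 16.4% to 0.3 × 0.9 + 0.7 × 0.10 = 34%.

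If the only error is over-reporting, specificity is 1 and the reported share is p × sens, which cannot exceed the truth.

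For the dose subgroup, let h be the true share of high users and r the share of low users who report high use. If misreporting is unrelated to outcome given true use, the retained contrast is h ÷ (h + (1 − h) × r).
- h = 0.5: 0.5/0.55 = 91% at r = 0.1, and 0.5/0.70 = 71% at r = 0.4.
- h = 0.7: 0.7/0.73 = 96% at r = 0.1, and 0.7/0.82 = 85% at r = 0.4.

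These figures show how the error would act. They do not estimate its size in this trial.

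**The case against.** **The article is condensed.** Grading of blackening and handling of leftover rolls could sit in the operating procedures or the pilot-tested case report forms, which are not shown. This stands in part: nobody can say that grading is absent from the trial. But the article does state its method of verification, and a graded soot scale would still not be a count.

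**A stronger reading is tempting.** A reader might infer that soot cannot resolve these cuts because it saturates, and that the counts are unverified. The documents support neither. They say nothing about how soot builds up or how well it can be read, exchanging boxes at visits limits carry-over, and a check does exist. The supportable statement is that its resolution at the cuts is not shown.

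**Adjacent counts are a severe test.** Many patients may lie well away from 8 a month or 3 a week, and a rough check may suffice for them. This is fair. It narrows the concern to patients near a cut and to those who inflate moderately.

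**The motive is not demonstrated.** Supply is a default amount, and the cash rewards depend on completing the 6- and 12-month visits, not on sessions. That weakens the case for deliberate inflation but does not remove the wish to appear diligent. The direction of error is plausible, not established.

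**Other safeguards exist.** The data monitoring committee looks for wrongly reported or missing data. However, the article describes no independent source of session counts for it to compare with.

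**Conclusion.** The concern holds in a limited form. Session counts rest on self-report plus a visual check with no stated grading or calibration, and two classifications with exact cuts depend on them.

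The reach is one secondary outcome and one subgroup. A reader might extend it to the main result, but the primary intention-to-treat comparison keeps patients in their chosen group and needs no session count. The article does not define the per-protocol population by sessions either, so no claim is made about those analyses.

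The size of the error cannot be derived from the documents. A reader might want a simulated bias, but the distribution of true use, the degree of inflation and the detection rate of the soot check would all have to be invented. The point rests on how the count is obtained, on the stated cuts, and on the feasibility conclusion that the Discussion draws from compliance. It is a worthwhile and inexpensive improvement to the stated method, not a flaw that invalidates the trial.

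**What to change.** 1. Reconcile the suggested one roll per session (Interventions and co-interventions) with the monthly issue of 120 rolls and 4 boxes (Compliance enhancement). Until this is done, a roll count cannot be converted into sessions.
2. Extend the box-exchange rule so that patients also bring back unused rolls at each monthly visit.
3. Record on the case report form the rolls issued (including extra issues), returned and reported lost, and the patient's reported rolls per session.
4. Compute rolls used = issued − returned − lost. Use rolls used ÷ rolls per session as an upper-bound cross-check on reported sessions.
5. Report the poor-compliance proportion and the dose grouping twice: by self-report, and with each patient's sessions capped by the roll count. Keep soot as a plausibility flag for mismatches.

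**Cost.** A minute or two at visits already held, and a few form fields. Discarded or shared rolls mean that the count bounds use only from above, and the bound is only as good as the reported rolls per session and losses. Reported compliance may look less favourable.
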